### Study Sites

This study will proceed in urban and rural areas in the coastal and highlands regions of PNG. Most of the PNG population lives in rural areas (85%), and the economy is primarily agricultural. We selected the Momase region as the coastal region in our study. The Momase region is composed of 4 constitutional provinces with a population over 1.8 million (2011 census). Madang is one of the provinces in this region; it has a population of 493,906 (2011 census). The study will be conducted in urban and rural villages in Madang district.

The Highlands region is the most densely populated region of PNG, with 23% of the total PNG population (2011 census). This region is composed of 7 provinces. The Eastern Highlands province is in the central highland’s cordillera and has a population of 579,825 (2011 census). Goroka is the capital of this province. The study will be conducted in Goroka and in rural villages of the Lufa district. These study sites are culturally and linguistically diverse. Tok Pidgin is the lingua franca.

### Study Groups and Sampling

#### Community Members

The criteria for including community members in interviews and the cultural epidemiological survey are being aged between 18 to 65 years and being cognitively able and willing to participate. The study will be conducted in either English or Tok Pidgin and participants should be able to communicate in either of these languages.

#### In-depth Interviews

A purposive sampling strategy will be used for recruiting participants for in-depth interviews. The sample will be distributed equally among male and female participants (ie, a 50% gender distribution). Community members are key stakeholders in adhering to *niupela pasin* and providing meaning to vaccine acceptance and demand. Starting with exploring and understanding their views is therefore critical.

A collaborating team of research assistants at each study site will initially meet local communities in urban and rural sites to establish rapport. Community opinion leaders and leaders of formal and informal community groups will be contacted, and we will explain the purpose and anticipated value of the study. Further, we will request their participation and assistance to facilitate community participation. Engaging these urban and rural opinion leaders and enlisting their cooperation will facilitate the planning and implementation of in-depth interviews. We will interview church leaders from the selected study sites.

The team of research assistants will go from house to house in parts of the selected study area to identify potential participants and achieve the desired sample compositions of urban and rural and male and female participants. The team will explain the purpose of the visit, solicit potential participants’ willingness to participate in the study, and, if they agree, obtain their informed consent (one-to-one) in confidence and with due attention to privacy. A total of 48 in-depth interviews will be conducted (12 community opinion leaders, 24 community members, and 12 church leaders). All interviews will be audio-recorded. The duration of each interview will be approximately 30 to 45 minutes.

### Vaccine Acceptance Survey

A random sampling strategy will be used to select the participants for this survey. We plan to use either the voters’ list or household listings to randomize the sample at an individual level or use village maps to randomize households to select the eligible participants. This will be achieved in collaboration with the provincial health authority (PHA). However, randomization depends on the availability of these resources. Otherwise, a convenience sample will be selected from the urban and rural areas of the selected study sites, stratified by gender (with a 50% distribution) and age group (18-40 years and 41-65 years). Trained research assistants working in 2 teams will conduct the survey, one interviewing and the other responsible for maintaining the data records. Approximately 360 interviews will be conducted (180 in each of the two regions. We calculated the sample size at a 5% margin of error with a 95% confidence level and a 50% response distribution.

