### Quantitative Analysis

The epidemiological survey will be conducted on tablets with ODK software. All interviews will be uploaded electronically to Google Spreadsheets (Google Inc). The final data set will be downloaded as Excel spreadsheets. STATA/SE (version 16.1; Stata Corp) will be used for statistical analyses. A descriptive analysis will be conducted to summarize the important results. The sociocultural and demographic characteristics of the participants will be summarized. Illness-related questions, such as perceived causes, distress patterns, and help-seeking behaviors, will be presented and compared between different gender and age groups across study areas. The explanatory variables in this study will be social and cultural features of illness experience, meaning and behavior, and questions of awareness and use of the COVID-19 vaccines for prevention. Inferential analysis using regression models will assess the determinants of COVID-19 vaccine acceptance. Narratives of statistically significant factors will be reviewed to better understand their importance.

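### The survey's 5% margin is that of a simple random sample, but one route draws households and all routes use a limited set of villages and urban areas, with no design effect allowed for

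*Protocol article*

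**What the plan says.** The Vaccine Acceptance Survey section of the protocol article offers three ways to find participants, depending on what resources are available:

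- voters' lists or "household listings to randomize the sample at an individual level";
- maps, where the team would "use village maps to randomize households to select the eligible participants";
- failing both, a fallback: "Otherwise, a convenience sample will be selected from the urban and rural areas of the selected study sites".

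One sample size serves all three: "Approximately 360 interviews will be conducted (180 in each of the two regions". Its basis is given in one sentence: "We calculated the sample size at a 5% margin of error with a 95% confidence level and a 50% response distribution". No design effect is mentioned. The number of adults taken per household, and how they are picked, are not stated.

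Eligibility (Community Members) rests on "being aged between 18 to 65 years and being cognitively able and willing to participate" and on speaking English or Tok Pidgin, so a household can hold several eligible adults. Under Study Sites, fieldwork is confined to urban and rural villages of Madang district, to Goroka, and to rural villages of Lufa district. The number of villages is not given.

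For the analysis, the Quantitative Analysis section says "Inferential analysis using regression models will assess the determinants of COVID-19 vaccine acceptance", after which the narratives behind significant factors are revisited. It names neither a variance estimator nor weights.

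**The concern.** Margin, confidence level and response proportion are the only inputs to the sample size, and they are the inputs for a simple random sample of individuals. A household draw is a different design. It produces either unequal selection chances or correlated answers, depending on how many adults are taken. People from the same village or urban block may also answer alike, whichever frame is used.

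Two things are at stake. The first is the stated precision, which appears in this document and which the described designs would not deliver. The second is what can be repaired later. If the number of eligible adults and the village code are not captured at interview, no later analysis plan can reconstruct the weights or the clusters. That matters for a study of sociocultural determinants, because significant factors are singled out for further interpretation.

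**Working it through.** **Inputs from the article:** proportion 0.50, margin 0.05, 95% confidence (z = 1.96), n about 360 (Vaccine Acceptance Survey); several eligible adults per household are possible (Community Members).

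**Not in the article, so assumed and varied:** eligible adults per household, adults taken per household, interviews per village, and intraclass correlation (ICC).

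**1. The plan's own figure.** n = z²p(1−p)/d² = 1.96² × 0.25 / 0.0025 = 384.2, so 385 rather than 360. A finite population correction, n/(1 + (n−1)/N), reaches 360 only for N of about 5,700. With the populations of Madang ("it has a population of 493,906 (2011 census") or Eastern Highlands (579,825) it gives about 384. At n = 360 the margin is 1.96 × √(0.25/360) = 5.16 points, which is 5% only after rounding. The gap between 360 and 385 is a separate matter. Its relevance here is that there is no slack to absorb a design effect.

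**2. One adult per household.** The weight is the number eligible, m, so the design effect is E(m²)/[E(m)]².
- 1–3 adults (20/60/20%): 4.4/2² = 1.10
- 1–4 adults (15/40/25/20%): 7.2/2.5² = 1.15
- 1–6 adults (15/30/20/15/10/10%): 11.65/3.05² = 1.25

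**3. Several adults per household, or several people per village.** The design effect is 1 + (b−1) × ICC, with b people per cluster.

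**4. Effect at n = 360.** Margin = 5.16 × √(design effect); effective n = 360/(design effect); n for a 5-point margin = 384.15 × (design effect), rounded up.

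| Assumption | Design effect | Effective n | Margin (points) | n for 5 points |
|---|---|---|---|---|
| One adult, 1–3 eligible | 1.10 | 327 | 5.4 | 423 |
| One adult, 1–4 eligible | 1.15 | 312 | 5.5 | 443 |
| One adult, 1–6 eligible | 1.25 | 287 | 5.8 | 482 |
| Two adults, ICC 0.1 | 1.10 | 327 | 5.4 | 423 |
| Three adults, ICC 0.5 | 2.00 | 180 | 7.3 | 769 |
| 10 per village, ICC 0.01 | 1.09 | 330 | 5.4 | 419 |
| 20 per village, ICC 0.02 | 1.38 | 261 | 6.1 | 531 |
| 30 per village, ICC 0.05 | 2.45 | 147 | 8.1 | 942 |

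Each row takes one source alone. Household and village effects acting together would widen the margin further.

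**5. Bias if one adult is taken and weights are ignored.** Use the 1–4 mix and let acceptance change by s points per extra adult. The unweighted estimate is then off by s × (E(m²) − [E(m)]²)/E(m) = s × (7.2 − 6.25)/2.5 = 0.38s. For s = 0, 5 and 10 this gives 0, 1.9 and 3.8 points, so there is no bias when acceptance is unrelated to household size.

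**6. Regression.** If clustering is ignored, the variance of a coefficient is understated by up to 1 + (b−1) × ICC when the factor is constant within a village. The understatement is much smaller when the factor varies among people in the same village.

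**The case against.** The best defence is that the article is a condensed account. Weights, the variance estimator and the within-household rule commonly sit in a full protocol or analysis plan that is not shown. This defence holds for the analysis. A reader might infer that estimates will be unweighted with ordinary standard errors, but the Quantitative Analysis section commits to neither. It does not rescue the precision statement, which is made here for every route at once.

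Other stronger readings also go beyond the text:

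- **Household draw both unequal and clustered.** At household level these are alternatives. One adult gives unequal chances without household clustering. Taking all eligible adults gives clustering with equal chances within the drawn frame.
- **Whoever is at home is interviewed.** The article does not say this. Its wording implies a further selection step that it does not describe.
- **Village clustering as a fault of the map route.** It would affect the individual-level route too, and its size depends on how many villages are used and how they are chosen, neither of which is stated.
- **A false-positive rate of about 17% for the determinants.** The arithmetic is right at a design effect of 2: 2 × (1 − Φ(1.96/√2)) = 0.166. But that design effect is assumed, and the rate applies to a factor constant within villages. Most listed explanatory variables are individual answers about experience, meaning, awareness and use. Rural-urban setting, named for comparison in the Analysis Plan, is the clearest case where a large effect is plausible.

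**Conclusion.** The concern holds in a limited form. The article states a simple-random-sample precision for designs that need not be simple random samples. At 360 interviews the margin is 5.16 points before any design effect. It is about 5.4 to 8.1 points under assumed design effects of about 1.1 to 2.5. That range rests entirely on assumed household sizes, cluster sizes and intraclass correlations.

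The consequences for analysis are conditional. Standard errors would be too small only if the regressions ignore clustering, and mainly for factors that vary little within a village. Unweighted estimates would be biased only if one adult per household is taken and acceptance is related to household size. The change is worth making because the information it needs must be collected at interview.

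**What to change.** **At data collection**
- On the household route, let the ODK form pick one eligible adult at random and record the number eligible.
- On every route, record the village or block code.

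**In the analysis of the random routes**
- Apply selection weights where the household route was used.
- Cluster standard errors by village or block, using Stata's survey commands or cluster-robust errors with a small-sample correction.

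**In the precision statement**
- Quote the margin for 360 with an explicit assumed design effect and its source.
- For the convenience fallback, claim no design-based margin and no selection weights.

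**Cost.** The form gains a random pick and two fields. The Results section says the instrument was still to be refined and pretested before the survey, and ODK and Stata are already chosen. Intervals will be wider. Clusters will also be few: at 10 to 30 interviews per village, 360 interviews give 36 to 12 clusters. With four strata (region by urban-rural setting) that leaves about 32 to 8 design degrees of freedom, which limits how many factors one model can carry. Treating villages as sampled clusters is a further assumption unless they are chosen at random, and the report should say so.

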### Analysis Plan

The primary goal of the study is to clarify descriptive, comparative, and analytic accounts of explanatory models of COVID-19 and how they explain awareness, acceptance, and use of vaccines. Comparative analysis will focus on questions of gender and rural-urban features of the COVID-19 pandemic and determinants of anticipated acceptance or refusal of COVID-19 vaccines.

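### The stated inputs give 385 survey interviews, not about 360, and the calculation covers one pooled proportion although the analysis focuses on comparisons

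*Protocol article*

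**What the plan says.** Under Vaccine Acceptance Survey the article gives the size and allocation: "Approximately 360 interviews will be conducted (180 in each of the two regions". The next sentence gives the basis: "We calculated the sample size at a 5% margin of error with a 95% confidence level and a 50% response distribution". It mentions no finite population, design effect or allowance for non-response.

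The same section leaves the sampling method open. The preferred routes are random, with households as the units drawn from the maps: "We plan to use either the voters’ list or household listings to randomize the sample at an individual level or use village maps to randomize". If the lists or maps are not available, the plan changes: "Otherwise, a convenience sample will be selected from the urban and rural areas of the selected study sites". The balance by gender and age is attached to that fallback, in the same sentence: "stratified by gender (with a 50% distribution) and age group (18-40 years and 41-65 years".

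The analysis sections go beyond one overall proportion. Analysis Plan says: "Comparative analysis will focus on questions of gender and rural-urban features of the COVID-19 pandemic". Quantitative Analysis says that illness-related questions "will be presented and compared between different gender and age groups across study areas", and it adds regression models for the determinants of vaccine acceptance.

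**The concern.** All the inputs of a textbook formula are stated, and so is its result, but the two do not agree. A reader who repeats the calculation cannot reproduce 360 and cannot tell whether an input is missing, the number was rounded down, or the sentence describes a different calculation.

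The second part is a mismatch of purpose. The one precision figure given belongs to a single proportion in the whole sample. The questions the study sets itself concern differences by gender, residence and age, and the determinants of acceptance. For these the article gives no precision, and it is clearly lower than 5 points. Without that figure, a comparison that shows no clear difference may be read as evidence of similarity when the sample could not have shown a moderate difference.

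**Working it through.** **Inputs.** From Vaccine Acceptance Survey: margin d = 0.05; 95% confidence, z = 1.96; p = 0.50 (I read the response distribution as the anticipated proportion); planned n = 360, 180 per region.

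**1. Can 360 be reproduced?**

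n₀ = z² p(1 − p) / d² = 3.8415 × 0.25 / 0.0025 = 384.1, so 385. The planned number is 25 fewer: 25 / 385 = 6.5%.

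Other readings do not return 360 either:
- Wilson interval: 381
- two-sided 90% or one-sided 95% confidence: 271
- z rounded to 2: 400

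A different proportion would do it: p(1 − p) = 360 × 0.0025 / 3.8415 = 0.2343, so p is about 0.375 or 0.625. The article states 50%.

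**2. Finite-population correction.**

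n = n₀ / (1 + (n₀ − 1)/N). Solving for the N that gives 360:

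N = 360 × 383.1 / (384.1 − 360) = about 5,700.

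Study Sites gives province totals only. For Madang, "it has a population of 493,906 (2011 census"; for Eastern Highlands, 579,825. Either one, or their sum of 1,073,731, gives 384 when rounded up or to the nearest whole number, or 385 for the sum. These totals are not the sampling frame, however. The frame is people aged 18 to 65 in selected parts of Madang district, Goroka and Lufa district, and its size is not given. For illustration, a frame of 10,000 gives 370 and a frame of 20,000 gives 377.

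**3. What 360 delivers.**

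Margin = 1.96 × √(0.25 / n), simple random sampling, p = 0.5, no correction:

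| Group | n | Margin (points) | Relative to n = 360 |
|---|---|---|---|
| Whole sample | 360 | ±5.16 | 1 |
| One region, or one gender if evenly split | 180 | ±7.30 | 1.4 |
| One gender within one region | 90 | ±10.3 | 2.0 |

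**4. Comparisons.**

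Half-width of a difference = 1.96 × √(2 × 0.25 / n per group):
- 180 v 180: 1.96 × 0.0527 = ±10.3 points
- 90 v 90: 1.96 × 0.0745 = ±14.6 points

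Difference detectable with 80% power, two-sided 5%, starting from 50%:
- 180 v 180: 14.6 points (50% v 64.6%), so about 15
- 90 v 90: about 20.4 points

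The half-width for 180 v 180 is slightly above 10 points, so the power for a true 10-point difference is slightly below one half.

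**5. Clustering.** If households or villages are sampled as clusters, each margin is multiplied by the square root of the design effect. The documents give no value. Purely as an assumed range, 1.5 to 2.0 would turn ±5.16 into ±6.3 to ±7.3 points.

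**The case against.** The strongest reply is that nothing of consequence is wrong. The text says approximately, 5.16 rounds to 5, and a difference of 0.16 points will mislead nobody about the level of acceptance. That stands as an argument about size. It does not make 360 the result of the stated calculation.

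A second reply is that the authors may have applied a finite-population correction to a small frame. This cannot be excluded. A reader might infer from the province totals that no correction could explain 360, but those totals cover all ages and whole provinces and are not what will be sampled. What can be said is that the input needed to make the sentence true is not given.

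A third reply is that the article never promises 5 points per region or per comparison. That is correct, so the second part is a mismatch between the sizing basis and the planned analysis, not a false statement.

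Three stronger readings are tempting and not supported:
- **The regional and gender estimates are two to three times less precise.** Each is 1.4 times less precise than the overall estimate. Only smaller subgroups or differences reach a factor of 2 or more.
- **Published intervals will be too narrow.** The 5% is a planning figure. Published intervals would come from the collected data, and the article prescribes no variance formula. That detail may be left to a fuller document.
- **The survey is clustered by village, so village must be the sampling unit.** The article allows random selection of individuals, random selection of households, or a convenience sample. It does not describe villages as a randomly selected stage.

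**Conclusion.** The point holds at modest size: minor to should-fix. The stated inputs give 385, about 360 is planned, and 360 gives ±5.2 points overall. The more useful half is the mismatch with the analysis: ±7.3 points for a group of 180, and ±10.3 points for a difference between two such groups, with about 15 points detectable at 80% power.

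These figures assume simple random sampling, p = 0.5, no finite-population correction and complete response. The 180 per region is stated. The 50% gender split appears in the sentence on the convenience fallback, so 180 per gender under random sampling is an assumption. No urban-rural or age-group split is given. An uneven split would make those comparisons less precise than 180 v 180.

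**What to change.** Keep 360 and restate what it provides, for example:

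> With 360 completed interviews and a proportion near 50%, the 95% margin of error under simple random sampling is ±5.2 percentage points overall and ±7.3 points in a region or gender group of 180. A difference between two groups of 180 has a 95% half-width of about ±10.3 points, and about 15 points can be detected with 80% power. If households or villages are sampled as clusters, these margins widen, and standard errors will match the sampling actually used. If the convenience sample is used, no design-based margin of error applies.

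If a finite-population correction produced 360, state the frame size and its source instead of the uncorrected overall margin, and keep the sentences on groups, clustering and the fallback.

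The cost is a few sentences. No further participants are needed, and the stated precision becomes slightly less favourable.

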### Health Care Providers

Health care providers involved in either COVID-19 clinical management or public health–related pandemic control activities in the selected study sites will be interviewed. We will identify key informant health care providers during earlier stages of the study based on respondent-provided information that identifies health care professionals engaged in relevant activities.

This sample will be selected purposively, and a question guide will guide the in-depth interview. The rationale for using in-depth interviews is to allow health care professionals to share their experiences and views privately without having another person in the room. A total of 16 interviews will be conducted with clinicians, health extension officers, nurses, midwives, and community health workers in health facilities (government and church-based), including provincial hospitals and health centers of urban and rural study areas.

### Data Management and Analysis Plan

The study instruments were pilot-tested during training workshops for validity and feasibility. The interview guides for community members and health care workers were developed after consulting experts in the field and the literature. They were pilot-tested with potential participants for rigor and credibility. For the quantitative survey, we adapted an instrument developed by one of the authors for a vaccine acceptance study in India. After completing the qualitative component, we will further develop this questionnaire to ensure feasibility in the study context. This instrument will be tested for content and face validity. All the interview guides and initial questionnaires were developed in English and translated into Tok Pidgin. All instruments were then back translated to English for accuracy.

